## 1. Synopsis

The pandemic of a newly upcoming viral disease which is associated with COVID-19 puts the whole world's health system under pressure.

Patients suffering from this disease mainly develop respiratory symptoms, which can lead to severe acute respiratory distress syndrome (ARDS) necessitating ICU, admission in 10-20% of the cases admitted to hospital. In addition to these symptoms, patients show lymphopenia, cardiac symptoms and altered coagulation profiles. Although those patients are treated in the ICU the mortality is up to 20% due to multiorgan failure [1, 2]. The aim of this study is to show non-inferiority of flow-controlled ventilation [5, 6, 7] compared to standard (lung protective ventilation) [3, 4].

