### Aim of the study

This study aims to demonstrate the positive effects on oxygenation of flow-controlled ventilation compared to conventionally ventilated patients (pressure control ventilation) in patients suffering from ARDS associated with COVID-19.

[figure not shown]

Figure 3: Tritube, Ventinova Medical, Eindhoven, The Netherlands

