#### 4. Objectives

##### Primary outcome:

We choose as the primary endpoint arterial oxygen partial pressure ( $\text{PaO}_2$ ).

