## **9. Statistical Consideration and Data Analysis**

Power-calculation: In order to keep the total number of patients small we will match the patients according to age, co-morbidities inhaled oxygen fraction and we regard this investigation as a feasibility study. Therefore, the sample size calculation based on the assumption of an effect size (change in PaO2) of 1.5 SDS in the primary endpoint (PaO2), an intended power of 80%, an alpha error of 5% and an equal sample ratio results in n=7 patients needed to treat. However, to compensate for dropouts we will include 10 patients in each group, which means in total 20 patients.

Data analysis: Categorical data will be presented as number and percentage, while interval data will be presented by median and interquartile range (IQR). Normally distributed data will be analyzed by using two-tailed unpaired Students t-test. Continuous variables with skewed distribution will be analyzed using Mann-Whitney U testing and dichotomous variables by means of Fisher's exact test. A p-value <0.05 is considered significant. All data analyses will be done using SPSS version v26 (IBM Corp, Armonk NY, USA). Graphs will be constructed using GraphPad Prism (GraphPad Prism version 5.0a for Windows, GraphPad Software, San Diego CA, USA).

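### The synopsis aims at non-inferiority, but the other stated aim, the sample size and the test are for a difference, and no margin is given: unless FCV is significantly better, the synopsis aim has no decision rule

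*Protocol*

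**What the plan says.** The Protocol describes its purpose in three ways.

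- Section 1 (Synopsis): "The aim of this study is to show non-inferiority of flow-controlled ventilation", with standard lung-protective ventilation as the comparator.
- Section 3, under Aim of the study: "This study aims to demonstrate the positive effects on oxygenation of flow-controlled ventilation compared to conventionally ventilated patients". This is an aim of benefit. It names no test, sidedness or error rate.
- Sections 6 and 9 both call the trial a feasibility study. Section 9 links that label to keeping the sample small.

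Section 4 names the endpoint ("We choose as the primary endpoint arterial oxygen partial pressure") but states no hypothesis, so it does not settle which aim governs.

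The design figures are all in section 9. The sample size assumes an effect "of 1.5 SDS in the primary endpoint", with 80% power and 5% alpha, and "an equal sample ratio results in n=7 patients needed to treat". This is raised to 10 per group, 20 in total, to allow for dropouts. For the analysis, "Normally distributed data will be analyzed by using two-tailed unpaired Students t-test", with Mann-Whitney U for skewed variables and significance at p<0.05. The Protocol states no non-inferiority margin, one-sided hypothesis or rule that sets a confidence bound against a margin.

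**The concern.** Non-inferiority and benefit are different hypotheses about the same comparison. A non-inferiority claim succeeds when a confidence bound excludes a deficit as large as a pre-set margin. A difference claim succeeds when the interval excludes zero. Section 9 supplies the second rule and not the first, so a reader who starts from the synopsis cannot tell what result would meet the aim.

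The gap matters most when the two arms turn out similar, which is the case a non-inferiority aim exists for. The planned test would then usually give p≥0.05. Beside the synopsis wording, that could be taken as support for the aim, although with 10 patients per group it is compatible with a sizeable loss of oxygenation. The trial is an unblinded comparison of a new ventilation technique in moderate to severe ARDS, so a mistaken claim of this kind would carry weight.

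This is not detail that a protocol would normally leave to a statistical analysis plan. The aim and the basis of the sample size are protocol content, and they are stated here inconsistently. An analysis plan could adopt one aim only by departing from the synopsis or from section 3.

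**Working it through.** **Inputs.** From section 9: effect 1.5 SD, power 80%, alpha 5% (two-tailed test), equal allocation, 7 per group before and 10 per group after the dropout allowance. The stated 7 is read as per group, which the later 10 in each group supports. The Protocol gives no margin and no expected deficit, so both are assumptions below, shown as ranges. All differences are in SD units of PaO2.

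**1. Reproducing the plan's figure.** For a two-sided test of a difference between two means (normal approximation):

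n per group = 2 × (1.960 + 0.842)² / 1.5² = 15.70 / 2.25 = 6.98, rounded up to 7.

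This matches, so the trial is sized as a difference test. The same arithmetic would give 7 for non-inferiority only if the margin were 1.5 SD and the true difference zero. The Protocol presents 1.5 SD as an effect size, not as a margin.

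**2. Precision of the planned comparison.** The 95% CI half-width is t(0.975, 2n−2) × √(2/n).

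- n = 10: 2.101 × √0.2 = 0.94 SD
- n = 7: 2.179 × √(2/7) = 1.16 SD

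An observed difference of exactly zero with 10 per group would leave a deficit of up to 0.94 SD inside the interval.

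**3. Non-inferiority power with truly equal arms.** One-sided 2.5%, noncentral t with 2n−2 degrees of freedom and noncentrality margin × √(n/2):

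| Assumed margin (SD) | Power, n = 10 | Power, n = 7 |
|---|---|---|
| 0.25 | 7.6% | 6.3% |
| 0.5 | 18.4% | 13.6% |
| 0.75 | 35.5% | 25.2% |
| 1.0 | 56.2% | 40.6% |
| 1.5 | 88.7% | 73.1% |

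Solving for 80% power gives a margin of 1.32 SD with 10 per group and 1.63 SD with 7.

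**4. Patients needed per group for an assumed margin.** 80% power, true difference zero, one-sided 2.5%, normal approximation, n = 15.70 / margin², rounded up:

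- 0.25 SD: 252
- 0.5 SD: 63
- 0.75 SD: 28
- 1.0 SD: 16
- 1.25 SD: 11
- 1.5 SD: 7

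**5. Chance that the planned test is non-significant when FCV is truly worse.** Two-tailed t-test at 5%; the probability of p≥0.05 is one minus the noncentral t power:

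| Assumed true deficit (SD) | n = 10 | n = 7 |
|---|---|---|
| 0.5 | 81.5% | 86.1% |
| 0.8 | 60.5% | 71.9% |
| 1.0 | 43.8% | 59.4% |
| 1.5 | 11.3% | 26.9% |

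With 10 per group the probability exceeds one half only for deficits below about 0.93 SD.

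**The case against.** The strongest defence is that the two aims point the same way and are nested. A significant two-tailed result favouring FCV would also establish non-inferiority for any margin of zero or more. That stands, and it limits the point to results that fall short of significant benefit.

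It can also be said that the sample size and test agree with the section 3 aim, so the outlier is one sentence in the synopsis. This is correct and is why the repair is cheap. It does not remove the contradiction, because that sentence is an explicit statement of the study's aim.

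The feasibility label also bears on how much weight the comparison should carry. But the Protocol attaches no feasibility criterion to it, and the comparative aims, the power calculation and the significance test all remain. The label makes a non-inferiority claim harder to support, not easier.

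Three stronger readings are tempting and are not supported.

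- A reader might infer that the design could never show non-inferiority. It could at a very wide margin: power with 10 per group is 88.7% at 1.5 SD. The fault is that no margin is stated.
- A reader might infer that non-significance is likely whenever FCV is materially worse. That depends on the deficit. At 1.5 SD, the only effect size the Protocol names, it happens in about 11% of trials with 10 per group.
- A reader might infer that the sponsor intends to treat p≥0.05 as non-inferiority. The Protocol does not say so. The inconsistent wording only leaves room for it.

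**Conclusion.** The contradiction is real and should be corrected. The synopsis states non-inferiority, section 3 states benefit, and section 9 sizes and tests for a difference, with no margin or confidence-bound rule and under a feasibility label. Unless FCV is significantly better, the plan has no rule by which the synopsis aim can be concluded, and a non-significant result would not establish it.

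The interval width and the 1.32 SD margin show that 10 per group could support non-inferiority with adequate power only against a very wide margin. If dropouts reduce the groups to 7, the margin needed rises to 1.63 SD. The reproduction of n = 7, the half-widths and the non-significance rates use the Protocol's own test and group sizes. The power figures assume a one-sided 2.5% level and truly equal arms. The margins and true deficits are assumed ranges, and all figures after the sample-size reproduction assume normal data with a common SD.

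The documents do not settle whether superiority, non-inferiority or feasibility is the intended purpose. That choice is the sponsor's.

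**What to change.** State one aim, in the same terms, in sections 1, 3 and 4.

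**Cheap option, consistent with section 9.** Replace the non-inferiority wording in the synopsis with a two-sided difference (superiority) aim on PaO2 within a feasibility study. Add that p≥0.05 will not be read as non-inferiority or equivalence, and that the mean difference will be reported with its 95% CI. This is a wording amendment with no extra patients. The sponsor gives up a non-inferiority claim that the plan has no rule to support.

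**If non-inferiority is kept.** State and justify a PaO2 margin, give the confidence-bound rule that decides the claim, and restate what power the planned 10 per group gives against that margin. The cost depends on the margin. On the assumptions above, 80% power would need about 16 per group at 1.0 SD and 63 per group at 0.5 SD. If the sample stays at 10 per group, the Protocol should say plainly that power is about 56% and 18% at those two margins.

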### Methods:

After admission to the ICU, the patients will receive information about the study and informed consent will be taken. Upon reaching the criteria for moderate to severe ARDS (P/F ratio below 200 mmHg and PEEP above 5 cmH2O) the patients will be randomized. In the treatment group (group A) the ultra-thin ventilation tube will be placed through the existing tube. Then flow-controlled ventilation will be applied for 48 hours. In the other group (group B) ventilation will be performed according to the lung protective strategy. All other treatment will be unchanged.

Data-collection will be started 1 hour after initiation of the study.

Primary end point is PaO2.

## 2. Abbreviations and Acronyms

**COVID-19:** Coronavirus disease 2019  
**ARDS:** acute respiratory distress syndrome  
**FCV:** flow-controlled ventilation  
**PCV:** pressure-controlled ventilation  
**PEEP:** positive endexpiratory pressure  
**PaO2:** arterial oxygen partial pressure  
**BMI:** body mass index  
**SCC:** society of critical care  
**VCV:** Volume Controlled Ventilation  
**OD:** outer diameter  
**ID:** inner diameter  
**FiO2:** inhaled oxygen fraction  
**PaCO2:** arterial carbone Dioxide  
**FiO2:** inhaled oxygen fraction  
**BGA:** blood gas analysis  
**BNP:** brain natriuretic peptide  
**aPTT:** activated, partial throboplastin time  
**INR:** international normalized ratio  
**PT:** prothrombin time  
**CRP:** c-reactive protein  
**Il-6:** interleucine 6  
**ECMO:** extracorporeal membrane oxygenation  
**SOFA:** sequential organ failure score  
**PIP:** pressure during inspiration

### 3. Background

The pandemic of a newly upcoming viral disease which is associated with COVID-19 puts the whole world's health system under pressure.

Patients suffering from this disease mainly develop respiratory symptoms, which can lead to severe acute respiratory distress syndrome (ARDS) necessitating ICU admission in 10-20% of the cases admitted to hospital (SCC-guideline). In addition to these symptoms, patients show lymphopenia, cardiac symptoms and altered coagulation profiles. Although those patients are treated in the ICU the mortality there is up to 20% due to multiorgan failure [1, 2]. Currently, there is no proven therapeutic strategy next to symptomatic treatment.

Although the severely ill patients will need intubation and invasive ventilation according to ARDS treatment strategies including low tidal volumes and low end-expiratory pressures, not all patients recover their pulmonary function [3, 4].

Flow control ventilation (FCV) is a recently developed ventilation strategy which allows to keep the intrapulmonary pressures low while achieving optimal gas exchange [5]. It had been proven in animal models to improve pulmonary function and oxygenation [6] and in cases with ARDS [7].

Flow Controlled Ventilation mode is a unique ventilation technique in which inspiration as well as expiration are controlled i.e. actively performed. This is achieved by generating a continuous flow into the patient's lungs during inspiration or a continuous (negative) flow, sucking gasses out of the patient's lungs.

The continuous flow without ventilation pauses, results in linear increases and decreases in intratracheal pressures [Figure 1]. As a result, the mean airway pressure will be higher compared to conventional large bore Volume Controlled Ventilation or Pressure Controlled Ventilation (PCV). Therefore, the bronchiole and alveoli will be kept open during ventilation facilitating oxygen uptake to the blood. Moreover, the continuous gas flow enhances gas mixture in the lungs also improving gas exchange. Altogether, FCV results in more efficient ventilation as compared to conventional ventilation

[figure not shown]

techniques.

Figure 1 pressure volume curve in flow-controlled ventilation

Evone® is the only commercially available ventilator applying FCV ventilation mode, thus directing the inspiration as well as the expiration [Figure 2]. Evone's FCV® ventilation mode is based on a controlled inspiration and expiration flow from a set PEEP to a set peak pressure and vice versa. The inspiratory flow is continuously controlled by advanced mass flow regulators; the expiratory flow is controlled by regulated suctioning.

[figure not shown]

Figure 2: Evone, Ventinova Medical, Eindhoven, The Netherlands

Evone is to be used in combination with Tritube [Figure 3], an ultra-thin endotracheal tube (outer diameter 4.4 mm/ inner diameter 2.4 mm), enabling highly accurate intra-tracheal pressure measurements and securing the airway with an inflatable high volume – low pressure cuff because FCV ventilation requires a sealed airway. With an outer diameter (OD) of only 4.4 mm, Tritube® is an ultra-thin ventilation tube, intended to obtain endotracheal access to the airway and to ventilate an adult patient [Figure 3]. Tritube has three lumina: a ventilation lumen - with Murphy eye and an inner diameter (ID) smaller than 3 mm; a cuff lumen - to inflate and deflate the high volume, low pressure cuff; and an intra-tracheal pressure measurement lumen - for continuous intra-tracheal pressure measurements. Tritube (including its cuff) is completely manufactured of Polyurethane. Additionally, Tritube has a malleable stylet to facilitate intubation [8, 9].

### Aim of the study

This study aims to demonstrate the positive effects on oxygenation of flow-controlled ventilation compared to conventionally ventilated patients (pressure control ventilation) in patients suffering from ARDS associated with COVID-19.

[figure not shown]

Figure 3: Tritube, Ventinova Medical, Eindhoven, The Netherlands

#### 4. Objectives

##### Primary outcome:

We choose as the primary endpoint arterial oxygen partial pressure ( $\text{PaO}_2$ ).

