##### Secondary Outcomes:

- Minute volume
- Tidal volume
- Respiratory rate
- Intertidal tracheal pressure amplitude
- Peak airway pressure
- End-tidal  $\text{CO}_2$
- Chest wall compliance
- Respiratory resistance
- Inhaled oxygen fraction ( $\text{FiO}_2$ )
- Arterial  $\text{CO}_2$  ( $\text{PaCO}_2$ )
- Tube obstruction by secretion

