## 6. Study Methodology:

This is a prospective, randomized feasibility study in adult patients with proven COVID-19 associated ARDS. We define ARDS according to “Berlin” definition integrating the oxygenation index (P/F ratio), the level of PEEP and clinical findings [3, 4].

We will use an envelope method to randomize patients into the flow-control ventilation group (group A) while all other patients will receive standard treatment (pressure control ventilation-group B). Due to the nature of the investigation (we use a special device and tube) blinding of the study groups will not be possible. The study will be performed in HMC facilities hosting COVID-19 patients.

After admission to the ICU for COVID-19 associated respiratory disease, the patients (or their relatives) will be approached, informed about the study and if agreed informed consent will be taken. Upon intubation the severity of the disease will be assessed thrice daily. When the patient fulfils the criteria for moderate to severe ARDS (P/F ratio between 100mmHg and 200 mmHg with PEEP of minimal 5 cmH2O and below 100mmHg with a minimal PEEP 5 cmH2O, respectively) randomization will be performed. Hereafter the group A patients will receive the ultra-thin Tritube through the existing tube. This does not need exchange of the tube, so it does not generate additional risks for the staff in terms of aerosols.

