### Group A: Flow-controlled ventilation

For the safety of the staff, only the investigators will be in the room and perform the change to the Tritube. This will be done under full PPE.

Via the existing tube the ultra-thin Tritube will be inserted. For this purpose, the existing tube will be clamped, and the ventilator will be set on hold. Then the connector with the inlet for the tritube will be connected and the Tritube will be inserted. Hereafter, the clamp will be removed, and the ventilator will be re-started. Then the Tritube will be advanced, blocked and connected to the Evone-ventilator. The ventilator settings will be started with the pre-existing-PEEP and the standard ventilator will be set on hold. The upper pressure will be determined to achieve a tidal volume of 6 ml/kg lean body mass, while the respiratory rate will be set to maintain an arterial BGA?? above 7.2 pH.

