### Group B: standard care (pressure-controlled ventilation)

In this group the ventilator settings will be adjusted by the ICU team (respiratory therapist) in agreement with lung-protective ventilation strategy [3a,4].

All other treatment will be unchanged and according to our local policies/guidelines.

In all groups the first clinical data collection starts after 1 hour of initiation of the “new” ventilation strategy.

The study ends at 48 hours after insertion of the Tritube or if the patient deteriorates needing prone-positioning or ECMO therapy.

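### The primary endpoint is raw PaO2, and FiO2 is not constrained after randomisation, so the comparison of ventilation modes is confounded by the oxygen setting

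*Protocol*

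**What the plan says.** The protocol's purpose, under Aim of the study, is an effect of the ventilation mode on oxygenation: "This study aims to demonstrate the positive effects on oxygenation of flow-controlled ventilation". Section 4 then fixes the outcome: "We choose as the primary endpoint arterial oxygen partial pressure". The synopsis names the same endpoint, and section 9 sizes the trial on it, with an effect of 1.5 SD.

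On FiO2 and who controls it:

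- **Group A (section 6).** The text covers the starting PEEP, the upper pressure needed for a tidal volume target, and the respiratory rate. On starting, it says "The ventilator settings will be started with the pre-existing-PEEP and the standard ventilator will be set on hold". FiO2 is not mentioned.
- **Group B (section 6).** "In this group the ventilator settings will be adjusted by the ICU team (respiratory therapist) in agreement with lung-protective ventilation strategy". FiO2 is not mentioned here either.
- **Blinding (section 6).** "blinding of the study groups will not be possible".
- **Secondary outcomes (section 4).** The list includes "Inhaled oxygen fraction".
- **Section 5.** FiO2 and PEEP are recorded together with each blood gas, every 6 to 8 hours.
- **Section 9.** Patients are to be matched on age, co-morbidities and inhaled oxygen fraction. The tests are an unpaired t-test or a Mann-Whitney test, and no account of FiO2 is stated.

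The P/F ratio, which is PaO2 indexed to FiO2, is already used for the ARDS definition and for eligibility (synopsis, sections 6 and 7).

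**The concern.** Patients enter the trial on the P/F ratio, but the treatment is judged on PaO2 alone. PaO2 reflects the state of the lung and the oxygen fraction being delivered. It isolates the effect of the mode only if FiO2 is similar in the two arms when the blood gas is taken, or if the analysis takes FiO2 into account. The protocol secures neither after entry, and those who adjust the ventilator know the arm.

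Two errors can follow. If FiO2 is turned down as gas exchange improves, a real benefit of flow-controlled ventilation is hidden. If one arm runs at a higher FiO2 for any reason, PaO2 differs with no effect of the mode. A larger sample would cure neither, because the problem is bias and not imprecision.

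**Working it through.** **1. The protocol's own sample size.** Inputs from section 9: effect 1.5 SD, power 80%, alpha 5%, equal groups, two-tailed test.

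n per group = 2 × (1.960 + 0.842)² / 1.5² = 2 × 7.85 / 2.25 = 6.98, so 7.

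The stated 7 is reproduced by the normal approximation. An exact t-test calculation gives 8.06, so 9. Its power is 73.1% at 7 per group and 88.7% at the 10 per group to be enrolled. The sample size is therefore not the issue here. It shows that the trial is powered and tested on PaO2.

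**2. Where FiO2 is controlled.**

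| Stage | What the protocol provides |
|---|---|
| Entry | Matching on inhaled oxygen fraction (section 9) |
| Group A after randomisation | PEEP start, upper pressure/tidal volume and rate; nothing on FiO2 (section 6) |
| Group B after randomisation | Settings adjusted by the ICU team; nothing on FiO2 (section 6) |
| Analysis | Unpaired t-test or Mann-Whitney test; nothing on FiO2 (section 9) |

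Data collection starts 1 hour after the new strategy begins and runs to 48 hours. Every value that could serve as the endpoint is therefore measured when the protocol no longer constrains FiO2.

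**3. Masking.** By definition PaO2 = (P/F) × FiO2. The P/F and FiO2 values below are assumed, and P/F is treated as constant when FiO2 changes, which is a simplification.

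- Without benefit: 150 × 0.60 = 90 mmHg.
- With a 20% gain in P/F and FiO2 lowered: 180 × 0.50 = 90 mmHg.

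The gain is real (180/150 = 1.20) and PaO2 shows no difference.

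**4. False benefit.** Same simplification, no effect of the mode, P/F 150 mmHg in both arms:

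- 150 × 0.60 = 90 mmHg and 150 × 0.70 = 105 mmHg, a difference of 15 mmHg.

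The protocol gives no SD for PaO2, so a range is assumed. The last column is the chance that a two-sided t-test with 10 per group gives p<0.05, against a nominal 5%.

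| Assumed SD (mmHg) | 15 mmHg in SD units | Chance of p<0.05 |
|---|---|---|
| 10 | 1.5 | 89% |
| 15 | 1.0 | 56% |
| 20 | 0.75 | 36% |
| 30 | 0.5 | 19% |

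At an SD of 10 mmHg the artefact is as large as the whole 1.5 SD design effect. A smaller FiO2 difference of 0.05 gives 7.5 mmHg, and the chance then runs from 36% (SD 10) to 8% (SD 30).

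**The case against.** The best counter-evidence is the matching on inhaled oxygen fraction. It shows that FiO2 was recognised as a determinant of the result, and a reader who calls FiO2 wholly uncontrolled would be wrong. Section 9 also describes the effect as a change in PaO2, which may mean change from a matched start. Both points stand as far as entry goes. Neither reaches the period of measurement: a change from baseline still carries whatever happens to FiO2 after baseline. Section 9 also does not explain how the matching works alongside the envelope randomisation in section 6.

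Three stronger readings are tempting, and the protocol does not support them.

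- **That listing FiO2 as a secondary outcome shows it is expected to differ between arms.** Tidal volume and respiratory rate are in the same list, and group A has a stated target for the first and a stated criterion for setting the second. Being listed says nothing about expectation.
- **That the primary comparison cannot answer the question at all.** FiO2 is recorded with every blood gas, so PaO2 can be read beside it. The supportable statement is that PaO2 alone is confounded by FiO2.
- **That bias is equally likely in both directions.** Lowering FiO2 as gas exchange improves is a clear route to masking. For a false benefit the protocol suggests no specific mechanism; it only leaves the possibility open.

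It is also fair to say that an SAP could add an adjustment for FiO2, and that this is a 20-patient study described as a feasibility study. However, the protocol itself makes raw PaO2 the primary endpoint and powers the trial on it. FiO2 after randomisation may itself respond to the treatment, so covariate adjustment is a weaker repair than an indexed endpoint.

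**Conclusion.** The concern holds as confounding of the primary comparison. Raw PaO2 is fixed as the powered endpoint, FiO2 is balanced at most at entry, and nothing in the protocol constrains it or accounts for it when PaO2 is measured in an open-label trial. Following the plan as written can hide an effect of the mode on oxygenation, which is the more plausible error, or mimic one.

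The size cannot be derived from the protocol, which gives neither an SD nor any expected FiO2. Under the assumed values, a 20% gain in P/F can vanish entirely. An FiO2 difference of 0.10 with no effect of the mode can produce a significant result 19% to 89% of the time, for SDs from 30 down to 10 mmHg. These figures rest on P/F being constant across FiO2 and on a uniform FiO2 difference between arms. They show what is possible and do not forecast what will happen.

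**What to change.** Amend sections 1, 4 and 9:

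1. Make the P/F ratio the primary endpoint, with PaO2 and FiO2 taken from the same blood gas, at one stated assessment time within the 48 hours. Without a time, the endpoint would still be undefined, because blood gases recur every 6 to 8 hours.
2. Keep FiO2 as a secondary outcome and add PaO2 to that list.
3. Restate and justify the 1.5 SD assumption for P/F. At the same standardised effect the sample size does not change.
4. Report FiO2 and PEEP by arm at the same blood gases.

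**Cost.** No new data are needed, since all components are already recorded together. The work is an amendment plus a fresh justification of the effect size, for which the protocol currently gives no SD on either measure. P/F still depends partly on FiO2 and PEEP, and in group A PEEP is tied to its prior value only at the start; item 4 makes any such difference visible. This changes the endpoint definition only and proposes no clinical rule for setting FiO2.
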